We will combine the data already extracted, stored and cleaned from APTS with the additional data obtained from study sites for each participating baby, to determine which factors are most influential in reducing transfusion requirements. The specific objectives are, after adjustment for prior risk factors (listed below), to determine:

1. Whether the effect of the intervention (cord clamping) on the outcome (blood transfusions) is mediated by placental transfusion (measured by hematocrit (Hct)) as seen in Figure 1 (a, c) following the causal path X → M1 → Y, where X is the intervention, ICC or DCC, Y is the outcome, mediator M1 is placental transfusion, and M2 is initial severity of illness stability

2. Whether the effect of the intervention (cord clamping) on the outcome (blood transfusions) is mediated by initial severity of illness (respiratory support, sampling line yes/no and total duration number, blood pressure, cumulative blood sample volume) as seen in Figure 1 (b, c) following the causal path X → M2 → Y

3. Whether the effect of cord clamping intervention on the outcome (blood transfusions) is driven by multiple mediators (placental transfusion and initial severity of illness) as seen in Figure 1 (c)

4. Whether cording clamping intervention (ICC or DCC) has a direct effect on the outcome after accounting for the mediators as seen in all panels of Figure 1: X → Y.

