**Figure 1 FIG1:**
[figure not shown]
Diagrams of the possible causal mechanisms for the outcome (Y) based on the cord clamping intervention (X) (a) A single mediator model in which the intervention X (intervention – ICC or DCC) affects the outcome Y through the indirect path of the mediator M1 (placental transfusion) and via a direct path from X to Y. In this model, M1 is assumed to be independent of M2; (b) An independent mediator model in which the intervention X (intervention – ICC or DCC) affects the outcome Y through the indirect path of the mediator M2 (initial severity of illness stability) and via a direct path from X to Y. In this model, M2 is assumed to be independent of M1; (c) If M1 is not independent of M2 the assumptions of models (a) and (b) are violated and we need to instead apply a multiple mediator model in which the intervention (X) affects the outcome (Y) through both mediators (M1 and M2) and via a direct path X to Y. In model (c) it is assumed that M1 has an acyclic relationship with M2, i.e., M1 causally influences M2. Careful consideration is needed to determine the sequential ordering of this relationship, this is discussed in the data analysis plan. ICC: immediate cord clamping; DCC: deferred cord clamping Image credit: study author; concept from Imai and Yamamoto [21] and Lee et al. [22]

Ethical considerations

The protocol was approved by the Northern Sydney Local Health District Human Research Ethics Committee in November 2019 (Version 3.0, Reference 2019/ETH12819), the Mater Misericordiae Ltd Human Research Ethics Committee (Version 1.0, Reference HREC/MML/56247), the Mercy Health Human Research Ethics Committee (Version 2.0, Reference 2020-078), and the Southern Health and Disability Ethics Committee (Version 1.0, Reference 19/STH/195). The ethics committees have granted a waiver of consent. The study is conducted in accordance with the National Health and Medical Research Council Statement on Ethical Conduct in Research Involving Humans.

Study measures

Intervention

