Putative mediating variables will only be analyzed if they have been measured before the outcome and will be excluded if there is not adequate time and date information available. If the multiple mediator model is applied, careful consideration of timing information will be evaluated. If there is insufficient empirical information to conclude the causal ordering of mediators (M1 causes M2), we will adjust our analytic approach (as discussed in the analysis plan) and discuss any limitations.

Data Analysis Plan

The analysis will include all babies who were initially randomized in the APTS trial for whom we were able to obtain the relevant data and be based on intention-to-treat. All statistical analyses will be conducted in R version 4.1.3 (2022-03-10; R Foundation for Statistical Computing, Vienna, Austria). Descriptive characteristics for continuous data will be presented as means or medians, as appropriate, and categorical data will be presented as frequencies and percentages.

A model-based inference approach will be applied to estimate the average causal mediation effect (ACME), average direct effect (ADE), and the average total effect as recommended [23-25]. This approach will be applied with the R “mediation” package [26]. We will initially fit two models, one model with mediation as the dependent variable and intervention as the independent variable (mediator model), and a second model with the outcome as the dependent variable, and both mediation and intervention as independent variables (outcome model). To account for the clustering of multiples, estimates will be calculated with generalized estimating equations with a compound symmetric correlation structure to account for within subject correlations. Depending on the outcome (binary, count, skew) these will be modelled with the appropriate family and link functions.

A counterfactual framework will be applied to the mediator and outcome models to simulate the values of the mediator and outcome to estimate the potential values of the mediator. This process is used to estimate the ACME, ADE, and average total effects; 95%CI will be estimated with 1000 bootstrap simulations.

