We will apply single mediator models on both placental transfusion variables and initial severity of illness variables if mediators are statistically independent, as seen in Table 1. Independence will be tested using linear regression and any appropriate link functions. If both mediators are not statistically independent, we will investigate the possibility of multiple mediator models, which require an expanded framework for analysis [21]. Here we assume that initial severity of illness is causally related to placental transfusion. For this process, we will use the method developed by Imai and Yamamoto [21] to estimate the ACME and ADE. Following this, 95%CI will be estimated with 1000 bootstrap simulations. If theoretical and empirical timing data and sensitivity analyses suggest that M1 and M2 have non-causal correlation and may be affected by an unmeasured latent mediator, we will adjust our approach to estimate interventional direct and path-specific indirect effects [27,28].

**Table 1 TAB1:** Overview of all mediation models * These variables will only be explored if a sufficient number of babies had both M1 and M2 measured ICC: immediate cord clamping; DCC: delayed cord clamping; Hct: hematocrit; vol: volume; n: number; mech: mechanical; vent: ventilation; O2: oxygen

Model	X - Intervention cord clamping	M_1_ - Mediator 1 placental transfusion	M_2_ - Mediator 2 initial severity of illness	Y - Outcome blood transfusions
If M_1 _is statistically independent of M_2 _after adjusting for covariates:				
1.0	ICC / DCC	Peak Hct	-	Transfusions any/vol/n
1.1	ICC / DCC	Admission Hct	-	Transfusions any/vol/n
1.2	ICC / DCC	Day 1 Hct	-	Transfusions any/vol/n
2.0	ICC / DCC	-	Mech vent or Inspired O2	Transfusions any/vol/n
2.1	ICC / DCC	-	Sampling line total duration	Transfusions any/vol/n
2.2	ICC / DCC	-	Sampling line yes/no	Transfusions any/vol/n
2.3	ICC / DCC	-	Cumulative blood sample volume	Transfusions any/vol/n
2.4	ICC / DCC	-	Blood pressure	Transfusions any/vol/n
If M_1 _is not statistically independent of M_2 _after adjusting for covariates:				
3.0	ICC / DCC	Hct peak	Mech vent or Inspired O2	Transfusions any/vol/n
3.1	ICC / DCC	Hct peak	Sampling line total duration	Transfusions any/vol/n
3.2	ICC / DCC	Hct peak	Blood pressure	Transfusions any/vol/n
3.3	ICC / DCC	remaining Hct variables*	Mech vent or Inspired O2	Transfusions any/vol/n
3.4	ICC / DCC	remaining Hct variables*	Sampling line total duration	Transfusions any/vol/n

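### If the mediators test as independent, only one-mediator models are listed, so each model's direct effect still contains the other mechanism's path and is not the effect Objective 4 asks for

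*Protocol article*

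**What the plan says.** Labels here follow the Objectives and Table 1: X is cord clamping, M1 placental transfusion (hematocrit), M2 initial severity of illness, Y transfusion.

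- Objective 4 asks whether the intervention "has a direct effect on the outcome after accounting for the mediators as seen in all panels of Figure 1". The mediators are in the plural.
- Objective 3 asks whether the effect "is driven by multiple mediators (placental transfusion and initial severity of illness) as seen in Figure 1 (c").
- In the Figure 1 legend, panels (a) and (b) each contain one mediator. Panel (c), with both, is for the dependent case: "If M1 is not independent of M2 the assumptions of models (a) and (b) are violated".
- The Data Analysis Plan states the branch rule: "We will apply single mediator models on both placental transfusion variables and initial severity of illness variables if mediators are statistically independent". Otherwise, "If both mediators are not statistically independent, we will investigate the possibility of multiple mediator models".
- The outcome model is "a second model with the outcome as the dependent variable, and both mediation and intervention as independent variables (outcome model"). In Table 1 the other mediator's cell is a dash for models 1.0-1.2 and 2.0-2.4. Models with both mediators (3.0-3.5) stand only under the heading for dependence.
- The branch is chosen by a test: "Independence will be tested using linear regression and any appropriate link functions". Table 1 adds adjustment for covariates; X is not named among them.
- The Results section promises the total effect and the indirect effects. The Figure 3 legend, for the independent case, defines both ACME and ADE.

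**The concern.** Objective 4 defines a direct effect net of both mechanisms but points to panels that each account for only one. In the independent branch no listed model holds M1 and M2 together, so no listed model estimates the effect that the objective names. What each model reports as direct is everything that does not pass through its own mediator, including the other mechanism under study.

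The Introduction says that the relative roles of the two mechanisms bear on practice, for example on whether an early top-up transfusion is worth considering. A large ADE in the hematocrit models could be taken to mean that clamping acts by some unexplained route, when it may be the severity path. The meaning of the reported direct effect would also change with the result of a preliminary test.

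**Working it through.** The article gives no figure for this point to reproduce, so the check is algebra, an illustration and a simulation.

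**1. Algebra.** Let M1 = a1·X + e1, M2 = a2·X + e2 and Y = c·X + b1·M1 + b2·M2 + error, with e1 and e2 independent (mediators independent given arm). The total effect is TE = c + a1·b1 + a2·b2.

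Leaving M2 out and substituting for it gives Y = (c + a2·b2)·X + b1·M1 + noise. Hence:

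- M1-only model: ACME = a1·b1 (correct), ADE = c + a2·b2.
- M2-only model: ACME = a2·b2 (correct), ADE = c + a1·b1.
- Model with X, M1 and M2: ADE = c.

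**2. Illustration.** The total of -0.07 is the systematic-review risk difference in the Introduction. The split of -0.04 (M1), -0.03 (M2) and 0 (direct) is an assumption.

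- M1-only ADE = -0.07 - (-0.04) = -0.03, and 0.03/0.07 = 43%.
- M2-only ADE = -0.07 - (-0.03) = -0.04, and 0.04/0.07 = 57%.
- Joint model: 0.

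**3. Range over splits.** Large simulated samples used a linear probability outcome, baseline risk parameter 0.6, and unit-variance mediators shifted by 0.4 in opposite directions between arms. These values are assumptions. The paths were mostly set to a total near -0.10; the Discussion gives about 10% without saying absolute or relative, and absolute is assumed. Clipping of probabilities moves some results slightly from their nominal values.

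| True paths (M1, M2, direct) | ADE, M1-only | ADE, M2-only | ADE, joint | TE - ACME1 - ACME2 |
|---|---|---|---|---|
| -0.05, -0.05, 0 | -0.049 | -0.050 | 0.000 | 0.000 |
| -0.04, -0.04, -0.02 | -0.060 | -0.060 | -0.019 | -0.020 |
| -0.08, -0.02, 0 | -0.020 | -0.079 | -0.001 | -0.001 |
| 0, -0.10, 0 | -0.094 | 0.000 | 0.000 | 0.000 |
| -0.09, -0.09, +0.08 | -0.008 | -0.008 | 0.071 | 0.071 |

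The last row shows the error in the other direction: a real opposing direct effect nearly vanishes from both one-mediator models. A logit outcome with equal paths and no direct effect gave -0.051 and -0.052, against 0.000 jointly.

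**4. Consequence for a test.** In 2000 simulated trials of 1401 babies (the number enrolled in Australia and New Zealand, ignoring missing data and clustering), with the first row's paths and a true direct effect of 0, a 5% test of the direct effect rejected in 48% (M1-only), 49% (M2-only) and 5% (joint) of trials.

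**5. The branch test.** In the same trials the mediators were independent given arm. A regression of M2 on M1 flagged dependence in 29% of trials without X in the model and in 5% with X. The choice of branch therefore turns on whether X is conditioned on, which the article does not say.

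**The case against.** The best defence is that the independent branch is less bare than it looks. Each ACME is valid there, and the Results section commits to reporting the total and indirect effects, with a template showing several independent mediators. Two non-zero ACMEs would show that both mechanisms operate, so Objective 3 is answered in substance. As the last column of the table shows, TE - ACME1 - ACME2 recovers the joint direct effect, so Objective 4 is derivable too. A reader might infer that Objectives 3 and 4 cannot be answered in this branch; the document does not support that.

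This stands, with limits. The subtraction is not planned, and separate bootstraps give it no confidence interval. It needs approximate additivity and a common analysis set, and it is not unique across three hematocrit and five severity indicators.

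It can also be said that Objective 4 means only the direct arrow drawn in each panel. The wording allows that for a single panel, but not together with accounting for the mediators in the plural.

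Two further readings should be resisted:

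- That independence is the authors' preferred branch. It is merely listed first. The article also sets out the dependent case at length, and how likely either branch is cannot be known from it.
- That the ADE would be mistaken for a stem-cell mechanism outside the two studied. The Introduction places stem cells within placental transfusion, with more of them arriving as its volume rises.

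Nor are rows 3.0-3.5 a ready-made remedy. They pair one hematocrit measure with one of three severity indicators, omit two others, and assume that M1 influences M2.

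**Conclusion.** The point holds in this form: in the independent branch every listed model's ADE contains the other mechanism's path, and panels (a) and (b) cannot show the direct effect that Objective 4 defines. Independence of the mediators does not cure this.

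Under additivity, the excess in each ADE equals the whole effect through the omitted mediator. In the illustration that is 43% or 57% of the total effect where the truth is 0. The size depends on the assumed split; the existence of the error needs only that the omitted path is non-zero. Because severity indicators enter one at a time, a 2.x ADE also keeps whatever part of the severity path that indicator misses.

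The fault lies in a stated rule and a stated objective, not in detail that an article would leave to a fuller plan. It should be corrected before the analysis.

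**What to change.** 1. Whatever the independence test shows, fit an outcome model with X, M1 and M2 together. Where the mediators are judged independent, include no M1-to-M2 path.
2. Name in advance one primary hematocrit measure and one primary severity indicator for this model. Add rows for the severity indicators missing from 3.0-3.5: sampling line yes/no and, subject to the article's rule that mediators precede the outcome, cumulative blood sample volume.
3. Take the Objective 4 direct effect from this model, and also the comparison of the two indirect effects, with a bootstrap 95% CI for their difference.
4. Keep models 1.0-1.2 and 2.0-2.4, but label their ADE 'effect not through this mediator'.
5. In Objective 4, replace the reference to all panels of Figure 1 with a reference to the joint model.

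The cost is wording plus a few more model fits on data the study already plans to collect. The joint model is restricted to babies with both mediators recorded, and intervals may be wider. The direct effect also remains conditional on the indicators chosen to represent each mechanism, which the report should say.

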**Figure 1 FIG1:**
[figure not shown]
Diagrams of the possible causal mechanisms for the outcome (Y) based on the cord clamping intervention (X) (a) A single mediator model in which the intervention X (intervention – ICC or DCC) affects the outcome Y through the indirect path of the mediator M1 (placental transfusion) and via a direct path from X to Y. In this model, M1 is assumed to be independent of M2; (b) An independent mediator model in which the intervention X (intervention – ICC or DCC) affects the outcome Y through the indirect path of the mediator M2 (initial severity of illness stability) and via a direct path from X to Y. In this model, M2 is assumed to be independent of M1; (c) If M1 is not independent of M2 the assumptions of models (a) and (b) are violated and we need to instead apply a multiple mediator model in which the intervention (X) affects the outcome (Y) through both mediators (M1 and M2) and via a direct path X to Y. In model (c) it is assumed that M1 has an acyclic relationship with M2, i.e., M1 causally influences M2. Careful consideration is needed to determine the sequential ordering of this relationship, this is discussed in the data analysis plan. ICC: immediate cord clamping; DCC: deferred cord clamping Image credit: study author; concept from Imai and Yamamoto [21] and Lee et al. [22]

Ethical considerations

The protocol was approved by the Northern Sydney Local Health District Human Research Ethics Committee in November 2019 (Version 3.0, Reference 2019/ETH12819), the Mater Misericordiae Ltd Human Research Ethics Committee (Version 1.0, Reference HREC/MML/56247), the Mercy Health Human Research Ethics Committee (Version 2.0, Reference 2020-078), and the Southern Health and Disability Ethics Committee (Version 1.0, Reference 19/STH/195). The ethics committees have granted a waiver of consent. The study is conducted in accordance with the National Health and Medical Research Council Statement on Ethical Conduct in Research Involving Humans.

Study measures

Intervention

The intervention consisted of either immediate or delayed cord clamping (as assigned in APTS). Immediate clamping was defined as clamping the cord within 10 seconds of delivery. Delayed clamping was defined as clamping the cord at least 60 seconds after delivery, with the infant held as low as possible, below the introitus or placenta, and with no palpation of the cord. Variations in the protocol were allowed if they would aid the mother, baby, or both. If the baby was non-vigorous (heart rate <100 beats per minute, low muscle tone, or lack of breathing, or crying), clinicians were allowed to break protocol using their discretion. Cord milking was not part of the protocol for either intervention. Further details may be sourced from the original APTS publication [15].

Outcomes

The primary outcome is the proportion of babies receiving red cell transfusion (for restoration of hemoglobin or blood volume). The secondary outcomes are number of transfusions per baby, cumulative transfusion volume (mL/kg) per baby, and primary reasons for each transfusion.

Putative Mediators

M1: Indicators of placental transfusion to be assessed will be hematocrit (on admission, highest on the first day, highest in the first week collected before any postnatal transfusion).

M2: Indicators of initial severity of illness to be assessed will be cumulative blood sample volume collected throughout hospital stay (number of blood tests multiplied by hospital’s usual sample volume for each type of test), sampling line (umbilical arterial line or peripheral arterial line) - yes/no and total duration, mechanical ventilation or inspired O2, and blood pressure.

Sensitivity Analyses (For the Primary Outcome Analysis Only)

Sensitivity analyses will adjust for the following variables: gender, birth <27 weeks vs. ≥27 weeks, method of delivery (vaginal versus cesarean), intraventricular hemorrhage (IVH) (yes/no and grade III/IV yes/no), surgery for patent ductus arteriosus (PDA), necrotizing enterocolitis (NEC), and sodium in the first 24 hours of life. We will also test model assumptions relating to sequential ignorability and post-randomization confounding (discussed further in the data analysis plan).

Potential Confounders (Covariates)

The following covariates may be used for adjustment in the analysis: gestational age at randomization before birth and any oral iron supplement pre-transfusion.

Timing of Assessments

Putative mediating variables will only be analyzed if they have been measured before the outcome and will be excluded if there is not adequate time and date information available. If the multiple mediator model is applied, careful consideration of timing information will be evaluated. If there is insufficient empirical information to conclude the causal ordering of mediators (M1 causes M2), we will adjust our analytic approach (as discussed in the analysis plan) and discuss any limitations.

Data Analysis Plan

The analysis will include all babies who were initially randomized in the APTS trial for whom we were able to obtain the relevant data and be based on intention-to-treat. All statistical analyses will be conducted in R version 4.1.3 (2022-03-10; R Foundation for Statistical Computing, Vienna, Austria). Descriptive characteristics for continuous data will be presented as means or medians, as appropriate, and categorical data will be presented as frequencies and percentages.

A model-based inference approach will be applied to estimate the average causal mediation effect (ACME), average direct effect (ADE), and the average total effect as recommended [23-25]. This approach will be applied with the R “mediation” package [26]. We will initially fit two models, one model with mediation as the dependent variable and intervention as the independent variable (mediator model), and a second model with the outcome as the dependent variable, and both mediation and intervention as independent variables (outcome model). To account for the clustering of multiples, estimates will be calculated with generalized estimating equations with a compound symmetric correlation structure to account for within subject correlations. Depending on the outcome (binary, count, skew) these will be modelled with the appropriate family and link functions.

A counterfactual framework will be applied to the mediator and outcome models to simulate the values of the mediator and outcome to estimate the potential values of the mediator. This process is used to estimate the ACME, ADE, and average total effects; 95%CI will be estimated with 1000 bootstrap simulations.

We will apply single mediator models on both placental transfusion variables and initial severity of illness variables if mediators are statistically independent, as seen in Table 1. Independence will be tested using linear regression and any appropriate link functions. If both mediators are not statistically independent, we will investigate the possibility of multiple mediator models, which require an expanded framework for analysis [21]. Here we assume that initial severity of illness is causally related to placental transfusion. For this process, we will use the method developed by Imai and Yamamoto [21] to estimate the ACME and ADE. Following this, 95%CI will be estimated with 1000 bootstrap simulations. If theoretical and empirical timing data and sensitivity analyses suggest that M1 and M2 have non-causal correlation and may be affected by an unmeasured latent mediator, we will adjust our approach to estimate interventional direct and path-specific indirect effects [27,28].

**Table 1 TAB1:** Overview of all mediation models * These variables will only be explored if a sufficient number of babies had both M1 and M2 measured ICC: immediate cord clamping; DCC: delayed cord clamping; Hct: hematocrit; vol: volume; n: number; mech: mechanical; vent: ventilation; O2: oxygen

Model	X - Intervention cord clamping	M_1_ - Mediator 1 placental transfusion	M_2_ - Mediator 2 initial severity of illness	Y - Outcome blood transfusions
If M_1 _is statistically independent of M_2 _after adjusting for covariates:				
1.0	ICC / DCC	Peak Hct	-	Transfusions any/vol/n
1.1	ICC / DCC	Admission Hct	-	Transfusions any/vol/n
1.2	ICC / DCC	Day 1 Hct	-	Transfusions any/vol/n
2.0	ICC / DCC	-	Mech vent or Inspired O2	Transfusions any/vol/n
2.1	ICC / DCC	-	Sampling line total duration	Transfusions any/vol/n
2.2	ICC / DCC	-	Sampling line yes/no	Transfusions any/vol/n
2.3	ICC / DCC	-	Cumulative blood sample volume	Transfusions any/vol/n
2.4	ICC / DCC	-	Blood pressure	Transfusions any/vol/n
If M_1 _is not statistically independent of M_2 _after adjusting for covariates:				
3.0	ICC / DCC	Hct peak	Mech vent or Inspired O2	Transfusions any/vol/n
3.1	ICC / DCC	Hct peak	Sampling line total duration	Transfusions any/vol/n
3.2	ICC / DCC	Hct peak	Blood pressure	Transfusions any/vol/n
3.3	ICC / DCC	remaining Hct variables*	Mech vent or Inspired O2	Transfusions any/vol/n
3.4	ICC / DCC	remaining Hct variables*	Sampling line total duration	Transfusions any/vol/n
3.5	ICC / DCC	remaining Hct variables*	Blood pressure	Transfusions any/vol/n

Sensitivity analyses have been limited to a set of biologically plausible and clinically meaningful groups that will be explored by including them for adjustment with covariates, and with the introduction of interaction terms if appropriate. Missing data will be described, reasons for missing data will be explored, and the impact of missing data on conclusions about the treatment effect on the primary outcome will also be explored where possible (e.g., using sensitivity analyses and multiple imputation techniques).

Methodological Assumptions

The causal mediation approach assumes sequential ignorability: that the treatment effect on the outcome is not confounding and that the mediator effect on the outcome is not confounded. As treatment was randomly allocated to neonates, we will assume that the treatment-mediator relationship is not confounded. However, the mediator itself has not been randomized. Thus, unknown confounders may be driving a spurious effect in the mediator-outcome relationship. We will employ additional sensitivity analyses to estimate whether any mediation effects are sensitive to the violation of the assumption of sequential ignorability. To test the possibility of unmeasured confounders we will examine the correlation between residuals in the mediator model and the outcome model. If there is no correlation this would suggest there is no unmeasured confounding, if there is correlation between the residuals, an unmeasured mediator may be affecting both the measured mediator and the outcome. We will apply the method developed by Imai et al. and Tingley et al. [23,26] that uses sensitivity analyses to evaluate if the ACME estimate is sensitive to unmeasured confounding.

Post-randomization confounders are dependent on the treatment allocated, affect both mediator and outcome, and can corrupt the mediation estimate. In the context of the present trial, it is possible that non-adherence to the intervention is a post-randomization confounder. We are analyzing our data based on intention to treat principles; however, a sensitivity analysis based on the actual time of cord clamping to assess the influence of non-adherence with the treatment protocol on our estimates may be performed.

